### Rejection criteria

Rejection criteria include:

1. Misdiagnosis.

2. The trial drug is taken at doses <80% or >120% of the requirement, or is not taken as directed.

3. Patients do not cooperate or cannot complete follow-up.

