### Concomitant treatments and forbidden drugs

Subjects will be permitted to continue concomitant treatment for comorbidities, such as hypertension, chronic bronchitis, stroke or skin disease, which will not affect the trial’s final results. However, they are forbidden to take any CM or Western medicine related to CNG, such as prokinetics, cholinergic agents, H2-receptor antagonists, proton pump inhibitors, mucosal-protective agents or antibiotics for the eradication of HP. Aspirin, nonsteroidal anti-inflammatory drugs, sedative hypnotics, antidepressants and opioids should be used sparingly. Each concomitant treatment should be documented strictly in the CRF, and once a subject is found to be taking forbidden drugs, he/she will be withdrawn from this study.

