### Outcome measurement

#### Primary outcome

The eradication of epigastric pain is considered the primary outcome to evaluate therapeutic effects. The visual analogue scale (VAS) score (0 to 10 numeric pain intensity scale) for epigastric pain was measured at every visit, ranging from 0 to 10, where a score of 0 suggests no epigastric pain and a score of 10 indicates the most severe epigastric pain. The eradication of epigastric pain is defined as a score of VAS that stops rising after dropping to 0 during the study. The eradication rate of epigastric pain will be compared among the three groups, together with the change in VAS scores before and after treatment in each group.

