#### The change in the patient-reported outcome instrument for chronic gastrointestinal diseases

Although the symptoms of chronic gastritis are not specific, the relief of clinical symptoms remains a major therapeutic aim. The patient-reported outcome (PRO) instrument for chronic gastrointestinal diseases (http://www.proqolid.org/) [20], a 6-dimension, 35-item instrument, will be performed on visits one and six, and the results will be used to compare the two visits to assess any changes in quality of life. The 35 items of the instrument are the following: fatigue, disturbed sleep, no hunger sensation, decreased appetite, afraid of society, dry mouth or bitter taste in mouth, bad breath, pharyngeal foreign body sensation, acid regurgitation, hiccup or belching, nausea or vomiting, burning pain behind the sternum, retrosternal pain, stomachache, gastric distension, gastric discomfort, stomach burning, abdominal pain, abdominal distension, degree of retrosternal pain, degree of heartburn, degree of stomachache, degree of gastric distension, degree of abdominal pain, degree of abdominal distension, diarrhea, constipation, incomplete sensation after defecation, defecation urgency, weight loss, emotional fluctuation, anxiety or nervous, worry about disease, impact on social activities and impact on family status and function. All of the items fall into five levels, which are scored as 0, 1, 2, 3 or 4, except for decreased appetite, which is grouped into four levels and scored as 0, 1, 2 or 3. The final score will be determined by the sum of all symptom scores.

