#### Sample size calculation

Based on the preliminary results of clinical research, no less than an estimated 55% total efficiency will be obtained with JWQTP treatment and approximately 30% will be obtained with the intervention of a placebo. Using a superiority test, no fewer than 66 subjects should be enrolled based on α = 0.05, β = 0.15 and power = 0.85 in each treatment group. Allowing for a 20% drop-out, we therefore propose the recruitment of a total sample size of 240 patients, with average distributions among the three groups.

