#### Statistical analysis

A full analysis set (FAS) is the primary analysis population for efficacy with an intention-to-treat principle. We estimate the missing data using the last observation carried forward (LOCF) method so that the population for the final analysis corresponds with that at the beginning of this study. The per-protocol set (PPS), in which all subjects enable themselves to finish the study according to the protocol, represents a subcardinal analysis population for efficacy. Descriptive statistics will be presented as the means, standard deviations, medians, minimum values and maximum values for continuous variables and as frequencies and percentages for categorical variables.

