An analysis of variance (ANOVA) or chi-square test will be used to compare baselines among patients, including demographic data, vital signs, history of diseases, basic treatment and so on. For the comparison of variations from the baseline to endpoint, Student’s t-test will be performed on variables with normal distributions, and the Wilcoxon rank sum test will be performed on variables with non-normal distributions. The evaluation of therapeutic effects will primarily be performed between baseline and visit six, in compliance with PPS, or the time to withdraw from the study, in compliance with FAS. In addition, the changes from baseline to visits two, three, four or five will be evaluated. For continuous variables regarding therapeutic effect, an ANOVA will be used for multiple comparisons of variation from baseline among different groups, and Dunnett’s tests will be used for comparisons within a group. A covariance analysis, adjusted for the baseline covariate, will be used to evaluate the differences of the symptom scores, VAS scores and PRO instrument scores among the groups considering the center effect. The least square mean in each group and the 95% confidence intervals of mean differences among groups will be calculated. The Cochran-Mantel-Haenszel test, stratified by center effect, and the logistic regression model, adjusted for covariates, will be used on categorical variables in addition to the chi-square test, Wilcoxon rank sum test or Fisher’s exact test. The total drop-out rate in each group will be compared with the drop-out rate due to AEs for drop-out analyses using chi-square test or Fisher’s exact test. For safety analyses, we will perform the chi-square test or Fisher’s exact test to evaluate the incidence rate of AEs among the groups and describe AEs using descriptive statistics through listing.

All statistical tests will be performed by an independent statistician using SAS 9.2, assuming a two-sided test and a 0.05 level of significance.

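### LOCF and evaluation at withdrawal let a patient who leaves after a single VAS of 0 count as eradicated, which can inflate each arm's rate and can bias the comparison in either direction

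*Protocol article*

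**What the plan says.** All references are to the protocol article.

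- *Primary outcome*: "The eradication of epigastric pain is defined as a score of VAS that stops rising after dropping to 0 during the study". No minimum duration, confirming visit or fixed time point is attached.
- *Statistical analysis*: the FAS, on the intention-to-treat principle, is the primary efficacy population. For missing values, "We estimate the missing data using the last observation carried forward (LOCF) method", so that the analysed population matches the one that started. The per-protocol set (PPS) is secondary.
- *Statistical analysis*, on timing: effects are evaluated from baseline to visit six in the PPS, "or the time to withdraw from the study, in compliance with FAS".
- *Rejection criteria*: one item reads "Patients do not cooperate or cannot complete follow-up". The others are misdiagnosis and drug intake below 80% or above 120% of the requirement or not as directed. The analysis set that such patients leave is not named.
- *Concomitant treatments and forbidden drugs*: "once a subject is found to be taking forbidden drugs, he/she will be withdrawn from this study".
- The patient-reported outcome (PRO) instrument "will be performed on visits one and six". Endoscopy and histopathology are likewise compared between visits one and six.

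**The concern.** The second half of the eradication definition, that the score does not rise again, can be checked only at later visits. LOCF with evaluation at withdrawal removes those visits for patients who leave. The same early 0 is thus judged by an easier test in a leaver than in a completer. The *Discussion* says that many patients have recurrent bouts of symptoms, so a single 0 is weak evidence of lasting relief.

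At stake is the primary result. The reported rate partly reflects when patients leave and in what state. If this differs between arms, so does the amount added to each rate. Two related matters need a sentence each: which set the rejection criteria apply to, and what LOCF means for outcomes measured only at the first and last visits.

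**Working it through.** **Inputs from the documents.** 240 patients at 1:1:1, so 80 per arm; 20% dropout; 55% v 30% (called total efficiency); power 0.85 (*Sample size calculation*); two-sided 0.05 (*Statistical analysis*).

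**Inputs not in the documents (assumed).** q, the share of dropouts whose last VAS is 0; dropout rates other than 20%; that 55% and 30% are eradication rates among completers.

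**1. The plan's own figure.** Two proportions, unpooled variance, two-sided: (0.55 × 0.45 + 0.30 × 0.70) × (1.960 + 1.036)² / 0.25² = 0.4575 × 8.978 / 0.0625 = 65.7, so 66 per group, as stated. Then 66 × 1.2 = 79.2, rounded to 80 per arm.

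**2. How far LOCF can move one arm.** With completer rate p and dropout d:

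- LOCF rate = p(1 − d) + qd
- Rate with dropouts counted as not eradicated (failure coding) = p(1 − d)
- The gap is qd. At d = 0.20, 16 of 80 patients are affected and each moves the rate by 1/80 = 1.25 points. As q runs from 0 to 1, the gap runs from 0 to 20 points.

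**3. Equal patterns in both arms.** p = 0.55 v 0.30, d = 0.20, q = 0.25 in both:

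- LOCF: 0.44 + 0.05 = 49% v 0.24 + 0.05 = 29%, difference 20 points
- Failure coding: 44% v 24%, difference 20 points

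Both rates rise, but the difference does not change.

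**4. Unequal dropout, q = 0.50 in both arms.**

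| Dropout, active v placebo | LOCF | Failure coding |
|---|---|---|
| 30% v 10% | 53.5% v 32.0% (21.5 points) | 38.5% v 27.0% (11.5 points) |
| 10% v 30% | 54.5% v 36.0% (18.5 points) | 49.5% v 21.0% (28.5 points) |

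Relative to failure coding, LOCF favours active treatment in the first row and placebo in the second.

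**5. Illustrative false-positive rates.** Equal completer rates of 30%, 20% dropout in both arms, 80 v 80, two-sided 0.05:

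- q = 50% v 10%: LOCF gives 0.24 + 0.10 = 34% v 0.24 + 0.02 = 26%, rejected in about 20% of simulated trials.
- q = 40% v 20%: LOCF gives 32% v 28%, rejected in about 9%.
- Failure coding gives 24% v 24%, rejected in about 5%.

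The 5% follows from the set-up: no true difference here means equal rates once every dropout is a failure.

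**6. Failure coding has its own weakness.** With equal completer rates of 30% but 30% v 10% dropout, it gives 21% v 27% and rejects about 14% of the time. LOCF with q = 50% gives 36% v 32% and rejects about 8%.

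**7. Outcomes measured at visits one and six only.** If a dropout has no exit assessment, LOCF carries the baseline forward and the change is zero. With 20% such dropouts in each arm, the mean difference is 0.8 × the completers' difference, a shrinkage of 20%.

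**The case against.** The strongest opposing case has five parts.

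- **A contradiction between rejection and intention to treat.** A reader might infer that the rejection criteria remove patients whom the FAS promises to keep. The text does not show this. The items read naturally as PPS exclusions, and FAS and PPS are evaluated separately. What stands is an ambiguity: the set is not named.
- **Certain bias, or a 20% false-positive rate.** A reader might conclude that the comparison is biased, or take 20% as the error rate. Neither is supported. Bias needs patterns that differ by arm, and the 20% rests on an assumed five-fold gap in q. The 20-point upper limit requires every dropout to leave at VAS 0, yet the first withdrawal criterion concerns worsening conditions, and such patients would probably leave with VAS above 0.
- **Forbidden drugs.** A reader might infer that a 0 recorded on a forbidden drug is carried forward as success. The protocol withdraws such patients but does not say whether a VAS taken after forbidden-drug use is kept. This is possible, not stated.
- **Zero change for every dropout.** This holds only without an assessment at withdrawal. The FAS is evaluated at withdrawal, and the visit schedule is a figure not shown, so an exit assessment cannot be ruled out.
- **The alternative is not free of bias.** Step 6 bears this out: failure coding can be the more sensitive rule when dropout is unequal. Nor does a visit-six definition confirm a first 0 at that visit, although it sets the same time point for everyone.

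The mechanism survives all five. The article itself fixes the endpoint definition, LOCF and evaluation at withdrawal, so this is a stated rule that works badly, not a detail left to an analysis plan.

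**Conclusion.** The concern holds in a limited form. Taken together, the stated rules score a patient who leaves after one VAS of 0 as eradicated, while a completer with the same early 0 must remain at 0. Relative to failure coding, the possible inflation is 0 to 20 points per arm at the planned dropout. The effect on the comparison is nil when dropout and q match across arms and can go either way when they do not. Its actual size cannot be derived because the documents do not give q; the rejection rates above only show sensitivity.

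This should be fixed, since it determines how the primary outcome is scored, but it does not invalidate the design. The points on rejection criteria and visit-six-only outcomes are clarifications.

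**What to change.** - Define eradication as VAS 0 at visit six with no VAS above 0 after the first 0.
- In the FAS of all randomised patients, count those without a visit-six VAS as not eradicated.
- Keep LOCF as a sensitivity analysis, with for example multiple imputation beside it, because failure coding is itself sensitive to unequal dropout.
- State that the rejection criteria define only the PPS.
- For outcomes measured only at visits one and six, do not carry the baseline forward where there is no exit assessment.

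Cost: wording only, and *Trial status* says that recruitment was still being prepared. The headline rates will be lower. If 55% and 30% are completer rates, 20% dropout gives 0.8 × 55% = 44% v 0.8 × 30% = 24%, with power of about 0.77 at 80 per arm. This compares with about 0.90 for 55% v 30%, which LOCF would reach only if dropouts left at VAS 0 as often as completers are eradicated. With q = 25% in both arms, LOCF power is about 0.74, so failure coding does not always cost power.

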## Discussion

To date, CNG remains unclear and has no specific remedy. The presence or absence and severity of dyspepsia have no obvious correlations with the histopathological findings and endoscopic grading of CG [3]. The therapeutic aim of CNG is to ameliorate these symptoms and to reduce the inflammation of the gastric mucosa, mainly focusing on the eradication of HP, prokinetics, antacids (H2-receptor antagonist or a proton pump inhibitor), mucosal-protective agents, anti-depression drugs and anti-anxiety drugs [5]. However, many CNG patients suffer from recurrent bouts of dyspeptic symptoms because these symptoms are easily influenced by psychological, social or dietary factors. TCM was more effective than chemotherapy in the treatment of chronic gastritis, including all subtypes, and no serious side effects have been identified. TCM has been widely considered an alternative option for chronic gastritis in East Asia [7,21]. According to the present findings, no scientifically rigorous trials have been designed to treat CNG patients with SSQDDSS. This study will be the first to explore the efficacy and safety of JWQTP and to provide evidence and an optimal dosage for a phase III clinical trial.

## Trial status

This trial is preparing for recruitment of participants at the time of manuscript submission.

## Abbreviations

AE: adverse event; AEF: adverse event form; AIDS: acquired immunodeficiency syndrome; ALP: alkaline phosphatase; ALT: alanine aminotransferase; ANOVA: analysis of variance; AST: aspartate aminotransferase; CFDA: The China Food and Drug Administration; CG: chronic gastritis; CM: Chinese medicine; CMTEI: Chinese medicine therapeutic effect index; CNG: chronic non-atrophic gastritis; Cr: creatinine; CRF: case report form; ECG: electrocardiogram; FAS: full analysis set; HP: *Helicobacter pylori*; JWQTP: Jian-Wei-Qu-Tong Pills; LOCF: last observation carried forward; PPS: per-protocol set; PRO: patient-reported outcome; SAE: serious adverse events; SD: syndrome differentiation; STB: serum total bilirubin; SSQDDSS: spleen and stomach qi deficiency with damp-heat stasis syndrome; TCM: traditional Chinese medicine; VAS: visual analog scale; γ-GT: γ-glutamyl transpeptidase.
